### Sample size

2.8

A power analysis is calculated before conducting this trial, which α = 0.05 and power = 90%. According to the previous pilot study, percentages of responders for the primary endpoint are verum 87.5%, sham 25%. Therefore, the sample size in this trial can be estimated initially according to the following formula. Each group needs at least 111 patients (assuming a 20% dropout rate), 333 patients in 3 groups totally will be enrolled in the study.

$$n=\frac{2{\left(u_{\alpha }^{'}+u_{\beta }\right)}^{2}p(1-p)}{{\left(p_{1}-p_{2}\right)}^{2}}$$

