**Discussion::**

This trial will be helpful in identifying whether acupuncture at compatibility acupoints is more effective than acupuncture at single acupoints.

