#### Outcome measurement

2.7.1

The primary outcome measure in this trial will be the PSQI, and the secondary outcome measures will include the sleep diary, Athens insomnia scale score, SF-36 score, ET results, and PSG results.

PSQI^[16,17]^ is a self-rated questionnaire that assesses sleep quality and disturbances over a 1-month time period. Nineteen individual items generate 7 “component” scores: subjective sleep quality, sleep latency, sleep duration, habitual sleep efficiency, sleep disturbances, use of sleeping medication, and daytime dysfunction. The sum of scores for these 7 components yields 1 global score. All patients will complete the PSQI 1 week before randomization and in the fifth and eighth weeks after randomization.

The sleep diary^[18]^ will be used to record the patients’ sleep and to collect sleep information to assess the therapeutic effect after treatment. Patients will need to complete the sleep diary every day during the treatment period and complete the CRFs only once a week.

The Athens insomnia scale will be used to record the patients’ self-assessment of sleep disorders. The items include sleep latency, waking up at night, waking up earlier than expected, total sleep time, sleep quality, emotions during the day, physical functioning during the day and daytime sleepiness. Patients will need to complete the Athens insomnia scale 1 week before randomization and at the fifth and the ninth week after randomization.

The SF-36^[19]^ questionnaire consists of 36 items containing 8 subscales each. These subscales consist of 2 higher-level summary scales, namely, the physical (physical function, physical role function, bodily pain, and general health) and psychological (vitality, social function, emotional role function, and mental health) summary scales. Patients will complete the SF-36 1 week before randomization and at the fifth and ninth week after randomization.

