#### Validity analysis

2.9.1

The efficacy scores for week 0, week 2, and week 4 for patients with primary insomnia will be calculated using the difference between the treatment period and baseline period. These indicators will be described by mean, standard deviation, median, P5, P75, and maximum and minimum values. PP and ITT will be used to analyze the main indicators and overall indicators. Because this study is a multicenter randomized controlled clinical trial, the central effect on the therapeutic effect will be considered in the analysis.

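### The 90% power in section 2.8 rests on a verum-versus-sham responder rate; it covers neither the PSQI score analysis nor compatibility versus single acupoints, and 111 per group does not follow from it

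*Protocol article*

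**What the plan says.** Section 2.8 (Sample size) is the only power statement in the protocol article. It sets the error rates ("which α = 0.05 and power = 90"%), takes its effect from a pilot study ("percentages of responders for the primary endpoint are verum 87.5%, sham 25"%), prints a two-proportion formula, and presents the size as its result: "Each group needs at least 111 patients (assuming a 20% dropout rate"), with a total given as "333 patients in 3 groups totally will be enrolled in the study". It does not say which acupoint group is meant by verum, and it assumes no difference between the two acupoint groups.

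Section 2.7.1 names the endpoint: "The primary outcome measure in this trial will be the PSQI". It describes a global score that sums seven components. Section 2.9.1 calculates efficacy scores "using the difference between the treatment period and baseline period" and describes them by mean, standard deviation, median and similar summaries.

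On purpose, the abstract's Background sets out to compare single with compatibility acupoints, and its Discussion says: "This trial will be helpful in identifying whether acupuncture at compatibility acupoints is more effective than acupuncture at single acupoints". The Introduction orders the aims differently: acupuncture against the non-acupoint control comes first, and single against compatibility second.

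**The concern.** A power figure belongs to one comparison, one endpoint scale and one assumed effect. Here the comparison is verum versus sham and the scale is a percentage of responders. The primary outcome is a score, and the question in the abstract concerns two active arms. A reader who sees one 90% figure for a three-arm trial could attach it to the compatibility-versus-single comparison, where nothing in the document supports it. A non-significant difference between the acupoint groups could then be taken as evidence that adding acupoints brings no benefit, when the trial may have had modest power to show one.

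**Working it through.** **Inputs from section 2.8.** p1 = 0.875, p2 = 0.25, α = 0.05 (sidedness not stated), power 90%, dropout 20%, 111 per group, 333 in total.

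**1. The plan's own figure.** The printed formula is n = 2(u_α + u_β)² p(1 − p)/(p1 − p2)². Take p as the mean of the two rates, (0.875 + 0.25)/2 = 0.5625.

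- Two-sided: 2 × (1.960 + 1.282)² × 0.5625 × 0.4375 / 0.625² = 13.24, so 14 per group. With 20% dropout, 14/0.8 = 17.5, so 18.
- One-sided: 10.79, so 11 per group, or 14 with dropout.
- Continuity-corrected, two-sided: 15 per group, or 19 with dropout.
- Strictest variant tried, two-sided α = 0.05/6: 20 per group, or 25 with dropout.

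None comes near 111. The two-sided result with dropout, 18, is about one sixth of it (18/111 = 0.16).

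**2. Power for verum versus sham at the stated size.** Evaluable per arm: 111 × 0.8 = 88.8, about 89. With the variance pooled under the null,

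power = Φ{ [|p1 − p2| − 1.96 √(2p(1 − p)/n)] / √[(p1(1 − p1) + p2(1 − p2))/n] }.

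For 0.875 versus 0.25 at n = 89 this is Φ[(0.625 − 0.146)/0.0578] = Φ(8.3), above 99.9%. So 90% does not describe this comparison either.

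**3. Compatibility versus single on the PSQI change.** The documents give no difference and no SD, so the result is in SD units (two-sided 0.05). The normal approximation is d = (1.960 + z_power) √(2/n); the t-test values are slightly larger.

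| Analysed per arm | 90% power | 80% power |
|---|---|---|
| 89 (after 20% dropout) | 0.486; t-test 0.49 | 0.420; t-test 0.42 |
| 111 (all analysed) | 0.435; t-test 0.44 | 0.376; t-test 0.38 |

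**4. The same comparison on the responder scale, for illustration.** The rate in the other arm is my assumption. Using the formula in step 2 with n = 89 and 87.5% in the better arm:

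| Other arm | Calculation | Power |
|---|---|---|
| 70% | Φ[(0.175 − 0.120)/0.0599] = Φ(0.91) | 82% |
| 75% | Φ[(0.125 − 0.115)/0.0578] = Φ(0.18) | 57% |
| 80% | Φ[(0.075 − 0.108)/0.0550] = Φ(−0.61) | 27% |

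Power reaches 90% when the other arm is at about 67.4%, a gap of about 20 points. If 87.5% is instead the single-acupoint rate, power is 42% against 95% and 72% against 97.5%, and 90% needs about 99%.

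**The case against.** The strongest reply is that the Introduction puts acupuncture versus control first, and sizing a trial on its first aim is an ordinary choice. That stands: the contrast in section 2.8 does serve a stated aim, and the section does not itself claim 90% for compatibility versus single. It does not rescue the figure. The scale still differs from that of the primary outcome, and the size still does not follow from the inputs.

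A second reply is that this is a condensed article, so a responder cut-off may sit in a fuller protocol or analysis plan. That also stands, and the absence of a definition is not the point here. The point is that the article ties its calculation to the primary endpoint on a scale other than the one on which it states that endpoint. A reader might go further and say that no binary analysis is foreseen at all. Section 2.9.2 prevents that, because it mentions logistic regression. It does so only as a means of covariate adjustment, however, and names no binary endpoint.

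A third, tempting inference is that the trial is underpowered for compatibility versus single at any plausible difference. The documents do not support it. A gap of about 20 points, or about 0.49 SD, would have 90% power, and nothing in the article shows such a difference to be implausible.

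**Conclusion.** The point holds in this form: the 90% figure describes neither the PSQI score analysis nor the compatibility-versus-single comparison, and 111 per group is not the 90%-power size for 87.5% versus 25%. The last part needs only the printed formula and inputs, and no choice tried for sidedness, continuity correction or multiplicity closes the gap between 25 or fewer and 111.

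How much power the trial has for compatibility versus single is open. The detectable differences assume two-sided 0.05, equal arms and an unadjusted comparison of two means. The responder-scale powers also rest on assumed rates. They show that power is well below 90% for gaps clearly smaller than 20 points; they do not show that the trial is too small.

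**What to change.** Rewrite section 2.8, leaving enrolment at 333:

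- Base the power statement on the PSQI score change used in the primary analysis, and name the time point. The abstract gives weeks 2 and 8 after randomization, section 2.7.1 gives weeks 5 and 8, and section 2.9.1 gives weeks 0, 2 and 4, so these must be reconciled first.
- Remove the claim that 111 per group is the 90%-power size derived from 87.5% versus 25%. Limiting the 90% to acupuncture versus control would not do, since it is wrong there too.
- State what 111 per arm delivers for compatibility versus single at two-sided 0.05: about 0.49 SD (90% power) or 0.42 SD (80%) with about 89 evaluable, and 0.44 or 0.38 SD if all 111 are analysed. Convert to PSQI points with an SD that the sponsor supplies and sources.
- Commit to reporting the compatibility-minus-single difference with its 95% confidence interval, and to not reading a non-significant result as equal efficacy.

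The cost is a redrafted section and a less favourable power statement for compatibility versus single. No further patients are needed.

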**Methods/Design::**

A total of 333 participants will be randomly assigned to 2 acupoint treatment groups or 1 nonacupoint control group in a 1:1:1 ratio by a central stochastic system. The acupuncture groups are: the single acupoint group: Shenmen (HT7); and he compatibility acupoint group: Shenmen (HT7), Baihui (DU20), and Sanyinjiao (SP6). The observation period of this trial will be 10 weeks. All patients will be followed for 1 week before randomization (baseline phase). After randomization, the patients will receive 30 minutes of electro-acupuncture once per day for 5 weeks. In the fourth week after the treatment, follow-up will be performed once. The primary outcome will be the Pittsburgh sleep quality index score at 1 week before randomization and 2 and 8 weeks after randomization. The secondary outcomes will include data from sleep diaries, Athens insomnia scale scores, ShortForm-36 Health Survey scores, electroencephalogram technology results and polysomnogram) results. Patients will be required to complete a sleep diary every day during the treatment period. Patients will also undergo electroencephalogram technology and polysomnogram 1 week before randomization and 5 weeks after randomization. The other secondary outcomes will be measured 1 week before randomization and 5 and 9 weeks after randomization.

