## Introduction

1

Insomnia is characterized by dissatisfaction with sleep quantity or quality and is associated with difficulty falling asleep and maintaining sleep.^[1]^ Most reports suggest that the prevalence rates of insomnia are 5% to 15%.^[2–5]^ Insomnia is a chronic problemand has been associated with erectile dysfunction,^[6]^ burning mouth syndrome,^[7]^ depression, ^[8]^anxiety,^[9]^ and functional gastrointestinal disorders.^[10]^ There are many ways to treat or relieve insomnia, including the “guided fantasy” technique,^[11]^ operation of a homeostatic sleep switch,^[12]^ and cognitive behavioral treatments.^[13]^ Among the dominant disciplines in traditional Chinese medicine, acupuncture and moxibustion are widely applied and promoted in clinical practice due to their safety and efficacy. Many Chinese and foreign studies have demonstrated that acupuncture has hypnotic effects and is effective in treating insomnia.^[14]^ However, questions related to the selection of acupoints to treat insomnia, as well as whether single acupoints or compatibility acupoints have better therapeutic effects, have affected clinical acupoint treatment, and these questions remain open.

Therefore, we will perform this multicenter, randomized, controlled, large-scale trial, first aiming to investigate whether acupuncture is effective in treating insomnia through a comparison with a non-acupoint control group. Second, we will compare the clinical efficacy of single acupoints with that of compatibility acupoints in the treatment of primary insomnia. The work reported in this article is financed by the National Basic Research Program (973 Program: 2014CB543100) in China and is registered with an identifier (NCT02448602) by Clinical Trials.gov in the United States of America.

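### The stated responder rates, alpha, power and formula give 14 patients per group (18 with dropout), not 111, and the basis of 111 cannot be established from the protocol

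*Protocol article*

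**What the plan says.** The Sample size section (2.8) sets out the whole calculation in one paragraph. It opens with "A power analysis is calculated before conducting this trial, which α = 0.05 and power = 90" per cent. It then takes from a pilot study that "percentages of responders for the primary endpoint are verum 87.5%, sham 25" per cent. It says that "the sample size in this trial can be estimated initially according to the following formula", and prints a per-group formula for comparing two proportions. The result is "Each group needs at least 111 patients (assuming a 20% dropout rate"), and 333 over three groups. The Abstract repeats the total and says that patients are "randomly assigned to 2 acupoint treatment groups or 1 nonacupoint control group in a 1:1:1 ratio".

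The Introduction gives two aims. The first is acupuncture against the non-acupoint control. For the other it says: "Second, we will compare the clinical efficacy of single acupoints with that of compatibility acupoints in the treatment of primary insomnia". The Abstract's discussion presents this second question as the one that the trial will help to settle. The Sample size section gives rates for verum and sham only.

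**The concern.** The paragraph offers 111 as the consequence of inputs that are all on the page, so it can be checked without any further document. A gap of 62.5 percentage points between responder rates is very large, and a two-group comparison of that size needs few patients. A requirement of 111 per group is out of proportion to it.

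Two things are at stake. First, the number that fixes enrolment has no justification that a reader can reproduce. Second, a reader who sees 90% power next to 111 per group will assume that the trial is sized for its questions. If the number does not follow from the stated effect, nobody can tell what difference the trial was built to detect. That matters most for single versus compatibility acupoints, where both arms receive active treatment and the difference may be much smaller than verum against sham.

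**Working it through.** **Inputs (Sample size, 2.8).** Alpha 0.05, sidedness not stated; power 90%; p1 = 0.875; p2 = 0.25; dropout 20%. The formula is

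n per group = 2 (u'α + uβ)² p(1 − p) / (p1 − p2)²

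The section does not define u'α or p. I take p as the mean of the two rates and u'α as the normal quantile for alpha, two-sided in the base case.

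**Attempt to reproduce 111.**
- p = (0.875 + 0.25)/2 = 0.5625, so p(1 − p) = 0.2461
- (p1 − p2)² = 0.625² = 0.3906
- (1.960 + 1.282)² = 10.507
- n = 2 × 10.507 × 0.2461 / 0.3906 = 13.24, so 14 per group
- With dropout: 14/0.8 = 17.5, so 18 per group and 3 × 18 = 54 in total

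The stated figures are 111 and 333. The ratio is 111/18 = 333/54 = 6.2.

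**Other readings of the undefined terms.**

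| Reading | n (formula) | Per group | With 20% dropout |
|---|---|---|---|
| Two-sided 0.05, 90% power | 13.24 | 14 | 18 |
| One-sided 0.05, 90% power | 10.79 | 11 | 14 |
| Two-sided 0.05/3, 90% power | 17.02 | 18 | 23 |
| Two-sided 0.05/6, 95% power | 23.11 | 24 | 30 |

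The meaning of p cannot rescue the figure either. Since p(1 − p) is at most 0.25, the formula at two-sided 0.05 and 90% power cannot exceed 2 × 10.507 × 0.25 / 0.3906 = 13.45. Other standard methods at two-sided 0.05 and 90% power give, before dropout, 12 (Fleiss), 15 (Fleiss with continuity correction), 8 (unpooled variance) and 14 (three-group arcsine). Dropout at 20% explains a factor of 1/0.8 = 1.25, not 6.

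**What 111 per group delivers for verum versus sham.** 111 × 0.8 = 88.8, about 89 evaluable. Inverting the printed formula, power = Φ(|p1 − p2| √n / √(2p(1 − p)) − 1.960). At the stated rates this is Φ(8.40 − 1.96) = Φ(6.44), above 99.99%.

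**What it delivers for single versus compatibility.** The section gives no rates for this comparison. For illustration only, assume that one arm responds at 87.5% and use 89 per group at unadjusted two-sided 0.05:

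| Difference | Other arm | Mean p | Power |
|---|---|---|---|
| 20 points | 67.5% | 0.775 | Φ(3.195 − 1.960) = 89% |
| 15 points | 72.5% | 0.800 | Φ(2.502 − 1.960) = 71% |
| 10 points | 77.5% | 0.825 | Φ(1.756 − 1.960) = 42% |

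**The case against.** The strongest defence has four parts.

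- **Initial estimate.** The section calls the calculation an initial estimate, which might leave room for a later increase. But it describes no adjustment except dropout, and still presents 111 as the consequence of the stated rates. Little of this stands.
- **Undefined terms.** The primed quantile and p are not defined, so it cannot be shown that no conceivable reading gives 111. This stands as a limit on the wording: what has been shown is that no standard reading comes near it.
- **Direction of the error.** For verum versus sham, 111 is far more than the stated effect needs, and 90% power is a chosen input, not a wrong result. This stands. That comparison is not endangered.
- **A condensed article.** An article may leave detail to a fuller protocol. That covers omissions, not a printed result that its own printed inputs contradict.

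A reader might go further and infer that 111 must rest on a hidden target difference of about 20 points. The document does not support this. With 89 evaluable per group, the printed formula (two-sided 0.05, 90% power) fits about 87.5% versus 67%, but equally about 48% versus 25%. Misprinted pilot rates, a slip in the calculation, or a number set on other grounds would fit as well.

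**Conclusion.** The sample-size statement is wrong as written. Its inputs give 14 per group, 18 with dropout and 54 in total, against a stated 111 and 333: a discrepancy of about six-fold. This rests on reading p as the mean rate and alpha as two-sided, but the conclusion does not depend on those choices, since the readings tried range from 14 to 30 per group with dropout. Either the rates, the formula inputs or the 111 is wrong, or 111 has a basis that is not stated. The document does not show which.

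Two consequences follow. The stated 90% does not describe the design for verum versus sham, where power at the stated rates is nearly 100%. And the stated rates give no basis for single versus compatibility acupoints, so the adequacy of the size for that question cannot be judged from this paragraph.

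It would be tempting to conclude either that 333 is excessive and should be cut, or that 333 is right and only its explanation is faulty. Neither follows. The verum versus sham rates say nothing about the second aim, and without the basis of 111 the total can be neither confirmed nor rejected.

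**What to change.** Correct the Sample size paragraph in one of these ways:

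1. If 111 came from a real calculation, state the inputs actually used: the comparison, both responder rates, alpha, sidedness and any multiplicity adjustment. Define u'α and p.
2. If a rate or the 111 is misprinted, correct it and show that the formula then returns the stated size.
3. If no original basis can be found, say that 333 was fixed on other grounds, and report what about 89 evaluable per group can detect, including for single versus compatibility acupoints, with the assumed rates labelled as illustrative.

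In every case, stop presenting 111 as the consequence of 87.5% versus 25%. Do not write in an effect solved backwards from 111 as if it had been the planning assumption.

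The minimum cost is the rewording of one paragraph, plus retrieving the original calculation. This finding does not by itself require a change in enrolment.

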### Statistical analysis

2.9

#### Validity analysis

2.9.1

The efficacy scores for week 0, week 2, and week 4 for patients with primary insomnia will be calculated using the difference between the treatment period and baseline period. These indicators will be described by mean, standard deviation, median, P5, P75, and maximum and minimum values. PP and ITT will be used to analyze the main indicators and overall indicators. Because this study is a multicenter randomized controlled clinical trial, the central effect on the therapeutic effect will be considered in the analysis.

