**Figure 2 (Continued) F3:**
[figure not shown]
Trial process chart.

The total observation period of this trial will be 10 weeks. All patients will be followed for 1 week before randomization (baseline phase). After randomization, the patients will receive 30 minutes of electroacupuncture once per day for 5 weeks. In the fourth week after the treatment, follow-up will be performed 1 time.

The single-blind evaluation method will be used in this trial. Nevertheless, the patients will be informed that they will be in either one of the acupoint treatment groups or the nonacupoint control group, which is the most effective way to avoid bias.

To communicate in a timely manner between each subcenter and to improve the efficiency of the trial, central randomization will be used, as performed by the China Academy of Traditional Chinese Medicine clinical evaluation center. The patients will be registered in the groups by phone or network at any time and any geographic location, such that the test manager can monitor the progress of each subcenter subject in real time.

This trial will be performed according to the principles of the Declaration of Helsinki (Version Edinburgh 2000). The trial protocol has been approved by the local institutional review board and ethics committee. Written informed consent will be requested from all participants before registration. All patients will be given enough time to decide whether they should sign the informed consent form, and they will be given treatment options other than acupuncture if they are not willing to participate.

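### The efficacy analysis names weeks 0, 2 and 4, which do not fit the weeks at which the primary PSQI is collected (5 and 8 in section 2.7.1, 2 and 8 in the abstract)

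*Protocol article*

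**What the plan says.** Section 2.9.1 (Validity analysis) of the protocol article defines the efficacy values: "The efficacy scores for week 0, week 2, and week 4 for patients with primary insomnia will be calculated using the difference". The contrast is "the difference between the treatment period and baseline period". No other analysis text names a week.

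The collection schedule is given elsewhere, in weeks after randomization:

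- PSQI (primary), section 2.7.1: "All patients will complete the PSQI 1 week before randomization and in the fifth and eighth weeks after randomization".
- PSQI, abstract: "The primary outcome will be the Pittsburgh sleep quality index score at 1 week before randomization and 2 and 8 weeks after randomization".
- Athens scale, section 2.7.1: "Patients will need to complete the Athens insomnia scale 1 week before randomization and at the fifth and the ninth week after randomization".
- SF-36, section 2.7.1: "Patients will complete the SF-36 1 week before randomization and at the fifth and ninth week after randomization".
- ET at weeks 3 and 5 and PSG at week 5, both section 2.7.1. The abstract gives ET at week 5 only.
- Sleep diary, section 2.7.1: "Patients will need to complete the sleep diary every day during the treatment period and complete the CRFs only once a week".

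Treatment is 25 sessions over 5 weeks (section 2.6). Section 2.1 adds one later visit: "In the fourth week after the treatment, follow-up will be performed 1 time".

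**The concern.** The analysis text and the collection schedule describe different time points. The analysis weeks stop at week 4 of a 5-week course, and a change limited to the treatment period has no place for the follow-up value.

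What is at stake is the identity of the primary comparison. If no stated analysis week coincides with a collected PSQI, someone must decide which collected visit stands in for week 2 or week 4. Made once data exist, that decision selects the primary endpoint. The values that bear on the full course and on durability (weeks 5, 8 and 9) have no stated analysis. The PSQI also looks back over one month (section 2.7.1), so a week 0 score would describe only time before treatment and a week 2 score would still include about two weeks of it.

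**Working it through.** The plan gives no figure to reproduce here, so the check sets the stated weeks side by side.

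**Timeline.** Baseline 1 week + treatment 5 weeks + 4 weeks to follow-up = 10 weeks, which agrees with the total observation period in section 2.1. End of treatment is therefore week 5 after randomization, and the follow-up visit is week 5 + 4 = 9.

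**Sessions completed, at 5 per week.** Week 0: 0. Week 2: 2 × 5 = 10. Week 4: 4 × 5 = 20. Week 5: 5 × 5 = 25. Counted from randomization, the last analysis week falls after 20 of 25 sessions.

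**Two readings of the analysis weeks.** Reading A counts from randomization: 0, 2, 4. Reading B counts from the end of treatment: 5 + 0, 5 + 2, 5 + 4 = 5, 7, 9.

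| Outcome | Post-baseline weeks collected | Match, reading A | Match, reading B |
|---|---|---|---|
| PSQI, section 2.7.1 | 5, 8 | none | 5 |
| PSQI, abstract | 2, 8 | 2 | none |
| Athens scale | 5, 9 | none | 5, 9 |
| SF-36 | 5, 9 | none | 5, 9 |
| ET, section 2.7.1 | 3, 5 | none | 5 |
| ET, abstract | 5 | none | 5 |
| PSG | 5 | none | 5 |
| Sleep diary (weekly CRF) | 1 to 5 | 2, 4 | 5 |

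**Results for the primary outcome.**

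1. Reading A with section 2.7.1: 0 of 2 PSQI assessments are used.
2. Reading A with the abstract: 1 of 2 is used (week 2). Week 4 has no PSQI.
3. Reading B with section 2.7.1: 1 of 2 is used (week 5). Weeks 7 and 9 have no PSQI.
4. Reading B with the abstract: 0 of 2 are used.

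PSQI week 8 is unused in all four combinations, and at most one of the three analysis weeks has a post-baseline PSQI. Treating week 0 as a label for baseline does not help: under reading A, weeks 2 and 4 still have no PSQI in section 2.7.1.

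**A second inconsistency underneath.** The two PSQI schedules disagree on the first post-baseline assessment (week 2 or week 5). Both put the last one at week 8, whereas the single follow-up visit falls in week 9, where the Athens scale and SF-36 are placed.

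**The case against.** The strongest defence has four parts.

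1. **The mismatch is not total.** This stands. The sleep diary gives weeks 2 and 4, and the abstract's schedule gives a week 2 PSQI. Under reading B the week 5 PSQI can be computed, and the Athens scale and SF-36 match at both of their visits, including follow-up. Reading B, however, sits badly with a contrast confined to the treatment period, and no instrument is collected at week 7.

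2. **Section 2.9.1 does not forbid other weeks.** This also stands. The sentence with the weeks leads into descriptive statistics, and the sentence assigning PP and ITT analysis names no weeks. But these are the only efficacy weeks the analysis text gives, so a reader has no other rule to follow.

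3. **Time-point detail may sit in an analysis plan that is not shown.** That would excuse silence. It does not excuse naming weeks that contradict the article's own schedule.

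4. **Weeks might be numbered from zero**, so that week 4 is the fifth week and week 2 the third. The article does not say so, and the abstract describes the fifth-week and ninth-week visits as 5 and 9 weeks after randomization. Even granted, this matches only the fifth-week PSQI and leaves the eighth-week one unused.

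A reader might go further and infer that no primary result can be computed on any reading. The documents do not support that, as the week 2 and week 5 matches show. A reader might also infer a measurable loss of power from analysing before the course is complete. Nothing in the article says how the effect builds up with sessions, so no power figure can be attached to this point.

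**Conclusion.** The point holds as a contradiction between the stated analysis weeks and the stated collection weeks. On the two natural readings, and on either PSQI schedule, the rule in section 2.9.1 cannot be carried out in full on the primary outcome: it uses 0 or 1 of the 2 post-baseline PSQI assessments and never the week 8 one. The consequence is an unfixed primary time point that would be settled after data exist, not an absence of any usable result. Data at weeks 5, 8 and 9 are collected and could be analysed; the text gives no rule for doing so.

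This rests on the article alone and on counting the follow-up visit as week 9 (5 + 4). It should be settled before unblinding because it determines which comparison is primary.

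**What to change.** Correcting section 2.9.1 alone is not enough, because the schedule it should refer to is itself inconsistent. In order:

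1. Reconcile the abstract and sections 2.1, 2.7.1 and 2.9.1 to one PSQI schedule: week 2 or week 5 for the first post-baseline assessment, and week 8 or the week 9 follow-up visit for the last.
2. In section 2.9.1, replace weeks 0, 2 and 4 with the collected weeks for each outcome. On the section 2.7.1 schedule these are weeks 5 and 9 for the Athens scale and SF-36, weeks 3 and 5 for ET (after reconciling with the abstract), week 5 for PSG, and weekly during treatment for the diary.
3. Name one primary PSQI time point. Neither PSQI schedule ranks its time points, so this is a choice the sponsor must make. The end-of-treatment assessment at week 5, after the 25th session, fits sections 2.6 and 2.7.1.
4. Make the follow-up PSQI a secondary time point, and reword the contrast so that the follow-up change from baseline is included.

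The cost is wording in four places and a dated amendment before unblinding. No extra patients are needed, and no extra visits, provided the reconciled schedule is the one already in use at the sites.
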